#### Days out of role

This brief questionnaire, administered at 6- and 18-month follow-up, consists of four questions assessing the number of days an individual is unable to attend to (or has some difficulty managing) normal activities (e.g., attending school, university or work) because of mental health problems. Questions were adapted from core items from the World Health Organization Disability Assessment Scale [95] to focus specifically on mental health.

#### Assessment of Quality of Life in four dimensions

The Assessment of Quality of Life in four dimensions (AQoL-4D) [96] is a standardised, self-report instrument designed to measure health-related quality of life across five domains: illness, independent living, social relationships, physical senses and psychological well-being. Each domain consists of three items; however, the illness subscale is not used for scoring purposes and therefore will not be collected during this trial. Some minor language adaptations were made to better suit the adolescent population (e.g., examples of household tasks were changed from ‘cleaning the house’ and ‘cooking’ to ‘cleaning your room’ and ‘helping with meals’). These adaptations were based on language in the AQoL-6D, a 20-item adolescent version of the same scale. The AQoL-4D has demonstrated sound psychometric properties, with reliability estimates ranging from 0.73 to 0.84 [97]. There is also some evidence to suggest that the AQoL is more sensitive than other health-related quality of life instruments to health states [98].

### Process variables

#### Expectation of success

At the pre-intervention assessment, participants will be asked a number of questions to determine their expectation of success associated with the intervention they are about to complete. These questions will assess (1) beliefs about internet treatments in general and (2) preference for trial condition. These questions are based on those used in previous research [99].

#### Acceptability of the intervention

At the post-intervention assessment, participants will be asked a range of questions designed to assess the acceptability and usability of the intervention they completed. These questions will measure how understandable and useful the program was, whether participants perceived that it affected their behaviour and whether they would recommend the program to others. Participants will also be provided with a list of techniques or skills specific to the program they completed (SPARX-R or lifeSTYLE) and will be asked which of these skills they have tried since completing the program and how helpful they were. These questions are also based on those used in previous research [99].

#### Adherence to the intervention

Participants’ adherence to their allocated intervention will be assessed using automated data collection through the SPARX-R and lifeSTYLE programs. For each participant, these data will include total number of visits to the site, average length of each visit and number of modules completed.

#### Reasons for non-adherence

Participants who are designated as non-completers of their allocated program will be asked to complete a brief questionnaire assessing their reasons for non-adherence to the program. These items are adapted from the Internet Intervention Adherence Measure [100], which was originally developed in the context of a paediatric encopresis intervention. The current items are similar to the adapted version of this measure developed by Farrer and colleagues [101] for use with an internet-based intervention for depression. Farrer et al.’s version of this measure includes two additional categories of reasons for non-adherence which may be relevant to the present trial: (1) engagement issues and (2) disease-specific issues (pertaining to depression).

### Parent outcomes

#### Patient Health Questionnaire-9

The Patient Health Questionnaire-9 (PHQ-9) is a self-administered nine-item depression screening and diagnostic tool based on DSM-IV criteria. The scale assesses the nine depression symptom criteria for frequency of occurrence during the previous 2 weeks, with scores ranging from 0 (not at all) to 3 (nearly every day). The psychometric quality of the PHQ-9 has been established [102].

#### Generalized Anxiety Disorder 7-item scale

The Generalized Anxiety Disorder 7-item scale is a widely used self-report anxiety scale which consists of seven items designed to measure the severity of symptoms of generalised anxiety disorder [103]. Participants rate individual statements on a 4-point frequency scale from 0 (not at all sure) to 3 (nearly every day) as they pertain to the previous 2 weeks. Individual item scores are summed to produce an overall score between 0 and 21, with higher scores indicative of greater anxiety. The scale was reported by its developers to have good reliability in addition to strong criterion, construct, factorial and procedural validity [103].

### Participant risk management protocol

All student participants will be given a contact sheet with the name and contact details of their school counsellor, as well as contact information for other counselling and support services (local and online). In addition, on each assessment occasion, participants’ responses will be monitored using an automated alert system that identifies severe mental health concerns, defined as endorsement of one or more items on the YRBS. Participants will be asked if they have experienced serious suicidal ideation or engaged in suicidal behaviour in the previous month. Endorsement of any item will trigger an alert whereby trial researchers will be notified immediately, prompting initiation of the study’s risk management protocol. The researcher will confidentially communicate the student’s name to the student’s school counsellor so that the counsellor can contact the student to offer immediate support. School counsellors of all participating schools will be briefed in advance about this risk management procedure. Students will also be provided with a popup alert via the online platform indicating that one or more of their responses suggest they may be distressed and encouraging them to seek support and/or use the contacts provided on their contact sheet. An email providing the same message will also be sent to their nominated email account.

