### Procedures

Immediately before the baseline assessment, during an allocated class period, school teachers will provide students with a URL that will take them to the trial registration page. Students will use their unique identification code to register at this page and set up a personal password. Students will also be required to provide a personal email address and mobile telephone number so that they can be contacted during the follow-up period after they have left school.

Students with parental and personal consent will complete questionnaires on three occasions during class time (pre-intervention, post-intervention and 6-month follow-up), as well as an additional 18-month follow-up questionnaire once they have graduated from secondary school. The timing of assessments was designed such that the 6-month follow-up will be conducted just before the trial HSC examination period, one of two major examination periods during the final year of school.

All assessments will be conducted via the online platform. Teachers will direct students to log on to the platform during the first three assessments, and participants will be emailed a link to log on directly from their personal computer on the final assessment occasion. All students will complete their allocated intervention (SPARX-R or lifeSTYLE) over the course of approximately 5–7 weeks in school via the online platform. Schools will timetable the intervention sessions to fit in with their respective schedules, but they will be advised to space sessions out so that students have sufficient time to reflect on the material presented in each module. On each assessment occasion, students who do not complete their assessments during the scheduled class time (owing to absence or other conflicting duties) will be asked to complete the questionnaires in their own time. A reminder email will be sent 1 week after the scheduled assessment, and a final reminder will be sent another week later to any student who still has not completed the scheduled assessment. Trial researchers will monitor completion of assessments and will remain in close contact with participating schools to ensure that school staff encourage assessment and intervention completion by all participating students. Students will no longer be able to access or complete assessments 1 month after their school’s scheduled assessment date.

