#### Youth Risk Behavior Survey

The Youth Risk Behavior Survey (YRBS) was designed to assess health risk behaviours among school students in years 9–12. For the purposes of the present study, the YRBS will be abbreviated to three items concerning suicidal thoughts, plans and attempts over the preceding month, for which participants will provide a yes-or-no answer. Endorsement of any of these items will trigger the trial’s participant risk management protocol (see below). Studies have shown that the suicidality items demonstrate both substantial reliability [71] and good convergent and divergent validity in high school samples [72].

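### The response to a suicidality alert is the same at every assessment, so at 18 months its only person-to-person step goes through the counsellor of a school the participant has left

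*Protocol article*

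**What the plan says.** The Youth Risk Behavior Survey section cuts the instrument to three yes-or-no items on suicidal thoughts, plans and attempts in the past month. "Endorsement of any of these items will trigger" the risk management protocol.

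The Participant risk management protocol section then sets out the procedure. Monitoring is introduced with "In addition, on each assessment occasion", and on an alert "trial researchers will be notified immediately". The researcher confidentially gives the student's name to the "school counsellor so that the counsellor can contact the student to offer immediate support". Preparation for this step is stated as follows: "School counsellors of all participating schools will be briefed in advance about this risk management procedure". Alongside it, the student sees a popup and receives an email, both encouraging help-seeking and use of the contact sheet. That sheet names the school counsellor and also lists other local and online services.

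Table 2 marks the YRBS at baseline, post-intervention, 6 months and 18 months. The Procedures section describes three questionnaires in class time, "as well as an additional 18-month follow-up questionnaire once they have graduated from secondary school". For the last of these, "participants will be emailed a link to log on directly from their personal computer on the final assessment occasion". At registration each student gives a "personal email address and mobile telephone number so that they can be contacted during the follow-up period after they have left school".

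**The concern.** The alert exists so that somebody reaches a young person who has just reported suicidal thoughts, a plan or an attempt. While participants attend school, the counsellor is the natural person to do this. At 18 months they have left. A researcher who follows the text as written would send the name to a counsellor who no longer has the participant at school and may have no current means of reaching them. It would also tell a person at a former school that an adult or near-adult school leaver had triggered an alert. What remains is the popup, the email and the contact sheet, all of which depend on the participant seeking help. The Procedures section foresees that participants will have left school and collects direct contact details for that reason, but the risk section does not tell the notified researcher to use them.

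This is a matter of participant safety. It does not bear on the estimate of effect.

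**Working it through.** The protocol states no figure to reproduce for this point. The check sets the sections side by side and adds one date calculation.

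**1. When can the alert fire?** By Table 2, the YRBS is given on four occasions: baseline, post-intervention, 6 months and 18 months. The risk section monitors responses on each of them.

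**2. Where is the participant on each occasion?** By the Procedures section, the first three are completed in class time. The fourth is completed after graduation, on a personal computer.

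**3. How long after school is the fourth?**
- Trial status puts baseline for the 2015 cohort in February 2015 and the 6-month wave in August 2015. February + 6 months = August, so follow-up is counted from baseline.
- February 2015 + 18 months = August 2016. This agrees with Trial status, which has the 18-month data collected in 2016.
- Trial design has the next academic year starting in February 2016, so Year 12 had ended by then. February 2016 to August 2016 is 6 months, so the gap since school is at least about 6 months.

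**4. Which parts of the response still work at 18 months?**

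| Step | In-school assessments | 18 months |
|---|---|---|
| Researchers notified | works | works |
| Researcher gives name to school counsellor, who contacts student | works | goes to the counsellor of a former school |
| Popup and email | work | work, if the participant acts on them |
| Contact sheet: school counsellor | works | out of date |
| Contact sheet: local and online services | works | works, if the participant acts on it |

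Only the second row has a person contacting the participant. It is also the only action the notified researcher is told to take.

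**5. Could the trial reach the participant another way?** Yes. It holds a personal email address and mobile number (Procedures). It also keeps a list linking emails to identification codes for use in case of risk (Data collection and management). The risk section sends an automated email but directs no personal contact through these details.

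**6. How many people are affected?** The count would be (respondents at 18 months) × (proportion endorsing a YRBS item). The second factor is nowhere stated, so the count cannot be derived. What can be stated is the share of occasions: 1 of 4.

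**The case against.** The strongest reply is that the phrase about each occasion belongs grammatically to the monitoring, and the counsellor step comes in a later sentence that speaks of students and their counsellor. On that reading the counsellor route describes only the school years, and the 18-month pathway is simply not described in a condensed article. The full risk management protocol is not shown, the Ethical approval section lists five approving bodies, and the contact details and risk-matching list suggest that direct contact was in mind.

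Part of this stands. The full protocol may contain a post-school route, and its absence cannot be inferred from one paragraph. But nothing in the wording limits the counsellor step to the school years: the sentence follows from endorsement of any item, at any monitored occasion, without exception. The point therefore rests on a rule the article states and that works badly at its own fourth assessment. It does not rest on missing detail.

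Three stronger readings are tempting, and the document does not support them:
- A reader might infer that nobody responds to an 18-month alert. Researchers are still notified, and the popup, email and non-school services remain.
- A reader might infer that suicidality is disclosed to the former school. The text has the name go confidentially to the counsellor, not to the school at large.
- A reader might take the expected number of 18-month respondents as the number at risk. That would count people answering, not people endorsing an item. It would also carry the attrition allowance of about 20 % in the Sample size section, set for a post-intervention effect, forward to 18 months. Applied to the roughly 300 per arm given for the interim analysis, it might deduct losses twice.

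**Conclusion.** The point holds for one of the four assessments. As written, the only person-to-person step after an 18-month alert is directed to the counsellor of a school the participant left at least about 6 months earlier, although the trial holds direct contact details. The response is weakened there but not absent. The three in-school assessments are unaffected, as are the primary contrast, power and type I error.

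The conclusion rests on reading the counsellor sentence as it stands, without an unstated limit to the school years. If the full risk protocol already holds a separate route for school leavers, the fault is only in the article's description and one sentence corrects it. The number of participants concerned is unknown. The change should be made on safety grounds, and Trial status shows the 18-month wave was still to come when the article was written.

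**What to change.** For the 18-month assessment only:
- Replace the counsellor step with prompt direct contact by the already-notified research team, using the mobile number and personal email given at registration. Limit this contact to signposting or handover to community and crisis services.
- List those services directly in the 18-month popup and email, so that they do not depend on a contact sheet issued at school.
- Tell participants of this route at the start of the 18-month questionnaire.
- Apply it identically in both arms. Leave the first three assessments as they are.

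If the full risk protocol already provides such a route, amend the Participant risk management protocol section to confine the counsellor step to the three in-school assessments.

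The cost is an ethics amendment (possibly to more than one of the five listed bodies), edits to the 18-month screens and email, and some existing-staff time during the one-month window in which the assessment stays open. No new data are needed. No new staff are needed provided the researcher's role stays at contact and signposting; clinical assessment by telephone would need people the document does not say the team has. Telling participants that the team may contact them could lower endorsement at 18 months, but the present procedure already passes names on and the route would be the same in both arms. The contact would follow the last scheduled assessment, so it would not alter a later outcome.

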### Data collection and management

All self-report data for the present trial will be collected via the online platform designed for and by the Black Dog Institute. Data collected routinely through the SPARX-R program will be passed to the online platform via an application programming interface. Data will be coded using a unique identification code. A list of emails associated with each identification code will be kept separately from the outcome database for the sole purpose of matching data to an individual participant in case of risk. Data will be stored securely on the university server, and only appropriate members of the TriPoD research team will have access to data collected in the context of this trial. All research personnel not involved with the day-to-day management of the trial will remain blinded to intervention allocation.

### Analysis

Primary analyses will be undertaken on an intention to treat basis, including all participants as randomised, regardless of treatment actually received. Effectiveness of SPARX-R will be established using a planned contrast of change from pre-test to the post-intervention in the active compared with placebo condition on the MDI within a mixed-effects model repeated-measures analysis [104]. School will be included in analyses as a random effect to evaluate and accommodate clustering effects. Variables used in determining allocation balance will be evaluated and retained in analyses where they are significant or quasi-significant. An unconstrained variance–covariance matrix will model within-individual dependencies. Transformation of scores, including categorisation, may be undertaken to meet distributional assumptions and accommodate outliers. Contrasts comparing change on the MDI from pre-test to other occasions of measurement will be undertaken as secondary analyses.

Models for binary outcomes analogous to the primary analysis approach will be used to compare the prevalence rates (MDD status) and other dichotomous outcomes between the two treatment arms at the endpoint and other occasions of measurement. Relative and absolute risk reduction, NNT (see [105]) and other relevant indices will be calculated for these outcomes and undertaken separately for participants who did not meet criteria for caseness at pre-test to assess the effect of the intervention on incidence. In analyses of scaled secondary variables, we will use methods comparable to those of the primary analysis. Subsidiary complier and related analyses will estimate the efficacy of SPARX-R in participants who completed modules from the SPARX-R program to produce a clinical impact (estimated to be four or more modules) [36]. In exploratory analyses, we will examine the effects of moderators and mediators of treatment (see [106]).

Interim analysis of outcomes of the 2015 cohort will be undertaken following the methods described above. Although the sample available will be of limited size, the outcome of this analysis will be used to guide the second stage of the trial, planned for 2016. Should there be clear evidence of lack of effect, based point estimates of effectiveness and associated confidence intervals, consideration may be given to abandoning second-stage recruitment or seeking possible modifications of the intervention.

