### Sample size

Depression has an estimated annual prevalence of 8.3 % in adolescents [12], and between 8 % and 20 % of young people in community samples develop depression over an 18-month period [51–53]. On the basis of the age of the current sample, together with the timing of the intervention (before a major, universal stressor), we expect that onset rates will be high (up to 15 %). Calculations of required sample size for the primary outcome measure were based on detecting a post-intervention effect size of 0.20 in combined analyses of data collected from 2015 and planned 2016 cohorts. This estimate is based on previous depression prevention research using an online intervention [54]. Although the expected effect is small, it reflects the universal nature of this intervention. Power was set at 0.80, α = 0.05 (two-tailed) and a correlation of 0.5 assumed between baseline and endpoint scores. To allow for possible clustering effects (i.e., participants from the same school having characteristics and outcomes more alike than between schools), a design effect [55] was calculated assuming an intraclass correlation coefficient (ICC) of 0.02 and an average class size of 25. The estimate of the ICC was derived from a previous Australian school-based study that found a non-significant ICC of 0.02 [54]. The estimated sample size was 1166. The target size sample size was set at 1600, or 800 students per condition, to accommodate an attrition rate of approximately 20 % (see [56]). This translates to approximately 50 students (or 2 classes) per school in 30 schools. An interim analysis of students in the 2015 cohort will involve approximately 300 students per arm. Under the assumptions outlined above, there will be 80 % power to detect an effect size of 0.40 standard deviations between groups.

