### Randomisation

Each participating school (cluster) will be randomised to complete the SPARX-R or lifeSTYLE program. School-level randomisation will be used to avoid contamination between conditions, for the ecological validity of providing the intervention at the cluster level and for practical convenience. A statistician not involved in the implementation of the trial will randomly allocate schools using the allocation sequence outlined below. The identity of schools will be concealed from the statistician during this process.

Randomisation in cluster randomised trials is problematic because the number of clusters involved is usually relatively small. In large, individually randomised trials, balance in the makeup of each arm is achieved as a function of the numbers involved. Balance between arms can be achieved by stratification or minimisation [57]. Stratification can accommodate only a limited number of balancing variables, and minimisation is based on incremental assignment of participants to groups. In TriPoD, the number of potentially relevant variables to be balanced between arms is quite large (e.g., sex, number of enrolled students, Index of Community Socio-Educational Advantage school index, language background other than English), and all available sites will be enumerated before commencement of the trial. Achieving approximately equal numbers of participants in each arm is also an aim of the allocation design, as this will determine the study’s power in the absence of substantial clustering effects. Accordingly, this attribute of each school will be used not to estimate the degree of balance, but rather to screen potential grouping after balanced combinations have been selected.

We will use the method developed and implemented by Carter and Hood [58] to ensure balance between intervention arms. This enumerates all possible divisions of the available schools into two groups and calculates a balance index [59] for each of these groupings. The 10 most balanced groupings will be retained after excluding any grouping resulting in a deviation of more than 10 % in predicted individual participant sample size between inventions. The allocation schedule will be selected at random from the groupings retained.

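### The primary pre-to-post change contrast on the MDI gains no precision from baseline at the assumed correlation of 0.5; constraining pre-test means equal would cut its variance by about a quarter, depending on how stable school effects are

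*Protocol article*

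**What the plan says.** The Analysis section defines the primary effect: "Effectiveness of SPARX-R will be established using a planned contrast of change from pre-test to the post-intervention" in the active arm against placebo, on the MDI, within a mixed-effects repeated-measures model. Pre-test is therefore one of the modelled occasions. Two features of the model are given: "An unconstrained variance–covariance matrix will model within-individual dependencies", and "School will be included in analyses as a random effect to evaluate and accommodate clustering effects".

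The only covariates mentioned are the balancing variables: "Variables used in determining allocation balance will be evaluated and retained in analyses where they are significant or quasi-significant". The examples in the Randomisation section are "sex, number of enrolled students, Index of Community Socio-Educational Advantage school index, language background other than English"; baseline MDI is not among them. Nothing says that pre-test means are taken as equal in the two arms. Scaled secondary outcomes are to be handled in a comparable way, later MDI occasions are also contrasted as change from pre-test, and the interim analysis of the 2015 cohort follows the same methods.

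The Sample size section plans for "detecting a post-intervention effect size of 0.20 in combined analyses", and states: "Power was set at 0.80, α = 0.05 (two-tailed) and a correlation of 0.5 assumed between baseline and endpoint scores".

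**The concern.** When each arm has its own pre-test mean and the data are complete, the change contrast from a repeated-measures model equals the plain difference in mean change. The unstructured covariance does not by itself bring the gain of baseline adjustment. That gain needs either equal pre-test means or baseline MDI as a covariate.

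Schools are randomised, so any difference between arms in mean baseline MDI is chance. The change contrast subtracts that difference with weight 1. The efficient weight is the regression of post-test on pre-test, which is 0.5 under the plan's assumption. The result is wider confidence intervals on the primary outcome than the collected data allow.

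This matters because the expected effect is small (0.20 SD) and the number of randomised units is modest. It matters most at the interim, where ten schools contribute and where point estimates and confidence intervals may lead to dropping the second stage.

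**Working it through.** **Inputs from the Sample size section.** Effect 0.20 SD; power 0.80; two-sided α 0.05; baseline–endpoint correlation r = 0.5; ICC 0.02; class size 25; target 1600 in 30 schools; attrition about 20%, so 1600 × 0.8 = 1280 analysed.

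**Reproducing 1166.** A two-sample t-test with d = 0.20 and variance 1.0 needs 394 per arm, 788 in total. The design effect is 1 + 24 × 0.02 = 1.48, and 788 × 1.48 = 1166. The stated figure is reproduced.

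**Variance factors at r = 0.5, in units of the single-score variance.**
- Post-test only: 1.00
- Change: 2(1 − r) = 1.00
- Baseline-adjusted: 1 − r² = 0.75

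The first two coincide, so 1166 fits either. The third would need 788 × 0.75 × 1.48 = 875. The planning therefore takes nothing from baseline. A simulation without clustering (394 per arm) gave an adjusted-to-change variance ratio of 0.756.

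The saving is 1 − (1 − r²)/(2(1 − r)) = (1 − r)/2: 35% at r = 0.3, 25% at 0.5, 15% at 0.7.

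**Power with the protocol's own design effect, 1280 analysed.** SE = √(4V/1280); power = Φ(0.20/SE − 1.96).
- Change: V = 1.48, SE = 0.0680, power 0.84
- Adjusted: V = 0.75 × 1.48 = 1.11, SE = 0.0589, power 0.92

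Applying one design effect to both factors is exact only if school-level effects at pre-test and post-test also correlate at 0.5.

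**Dependence on the school-level correlation.** Call it c. The article does not give it, so I take 0 to 1 as an assumed range. Let m = 1280/30 = 42.7 analysed per school, with ICC 0.02 on both occasions and total r = 0.5.
- Single-occasion variance: V = 0.98 + 0.02m = 1.833
- Pre–post covariance on the same scale: C = (0.5 − 0.02c) + 0.02cm
- Change: 2(V − C)
- Equal baseline means: V − C²/V
- Individual-level covariate with slope 0.5: 1.25V − C

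| c | C | Change | Equal means | Saving | Covariate | Saving | Power, change | Power, equal means |
|---|---|---|---|---|---|---|---|---|
| 0 | 0.500 | 2.667 | 1.697 | 36% | 1.792 | 33% | 0.59 | 0.78 |
| 0.5 | 0.917 | 1.833 | 1.375 | 25% | 1.375 | 25% | 0.75 | 0.86 |
| 0.8 | 1.167 | 1.333 | 1.091 | 18% | 1.125 | 16% | 0.87 | 0.93 |
| 1 | 1.333 | 1.000 | 0.864 | 14% | 0.958 | 4% | 0.95 | 0.97 |

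Power uses the normal approximation. The equal-means column assumes that the model represents the school-level covariance between occasions correctly.

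**The case against.** **Nothing is wrong as such.** The change contrast is unbiased under randomisation, and 1166 is correctly computed for it. That stands: the point concerns efficiency, not validity.

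**The text may be compatible with the efficient model.** A model with equal pre-test means also yields a pre-to-post contrast, and that parameterisation could be set out in an analysis plan that is not shown. This stands in part. If such a plan imposes the constraint, the point is already met. But the article does name its estimator and covariates, and its sample size takes no credit for baseline.

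**The saving is not a fixed 25%.** This stands. A single school intercept that is stable over time would cancel from the change contrast, and a simple covariate would then gain almost nothing. The equal-means model still gains at every value in the range.

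**Two stronger readings are tempting, and the documents support neither.**
- A reader might infer that true power is below 80%. With about 43 per school, power of the change contrast runs from 0.59 to 0.95 according to a correlation the article does not state; with the protocol's own 1.48 it is 0.84.
- A reader might equate a 25% saving with one third more students. With 30 schools fixed, 1707 students means 56.9 per school and a design effect of 2.12. Variance falls by only 13%, and power reaches 0.81 rather than 0.86.

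**Adjustment is not wholly free.** A covariate model drops students without a pre-test score unless it is imputed, which conflicts with the stated intention-to-treat set. The equal-means model avoids this, but it assumes equal true baseline means among consenting students. The article does not say whether consent preceded allocation.

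**Conclusion.** The point holds as a loss of precision in a valid primary analysis. At the plan's assumed r = 0.5, the change contrast is no more precise than a comparison of post-test means, although baseline MDI is already collected.

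Baseline adjustment would cut the variance by 25% if the school-level pre–post correlation is also 0.5. Across 0 to 1, the cut is about 36% to 14% with equal baseline means and about 33% to 4% with a simple covariate. These ranges rest on r = 0.5, ICC 0.02 on both occasions, and 1280 analysed in 30 schools.

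The change is worth making but is not essential to the trial's validity. The equal-means model is the better remedy, because it gains across the whole range and keeps students without a baseline score.

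**What to change.** In the Analysis section, keep the repeated-measures model, the school random effect and all randomised participants. Constrain the pre-test MDI mean to be equal in both arms, and name the resulting arm difference in MDI at post-intervention as the primary estimate. State how school effects are allowed to vary between occasions, since the size of the gain depends on it.

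Use the same form for the 6- and 18-month contrasts, for scaled secondary outcomes with a baseline, and for the interim analysis. Report the unconstrained change contrast as a sensitivity analysis. It does not need the equal-means assumption, so a marked disagreement would show where that assumption is in doubt.

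The cost is a few sentences of analysis wording and no new data. Under Trial status, the article reports that the 2015 post-intervention assessments are complete, so the change should be dated, entered on the registry with the other amendments, and made without sight of results by arm.
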